# Acute Adenosine Receptor Antagonism in Combination With Acute Intermittent Hypoxia to Promote Breathing Plasticity in Amyotrophic Lateral Sclerosis: Protocol for a Randomized, Double-Blinded, Placebo-Controlled Trial

**DOI:** 10.2196/76105

**Published:** 2025-11-07

**Keywords:** acute intermittent hypoxia, adenosine A2A receptor, amyotrophic lateral sclerosis, neuronal plasticity, respiration

## Abstract

**Background:**

Respiratory impairment is a major concern in amyotrophic lateral sclerosis (ALS), shortening survival and lowering quality of life. One therapy with promise to delay respiratory decline in ALS is acute intermittent hypoxia (AIH), consisting of alternating periods of breathing mildly hypoxic (9%-12% O_2_) and normoxic (21% O_2_) gas. AIH stimulates spinal, serotonin-dependent neuroplasticity in rodent models, conferring functional benefits in diverse physiological systems without detectable pathology. However, in rodent models, AIH-induced neuroplasticity is constrained by distinct signaling cascades initiated by spinal adenosine.

**Objective:**

We propose to investigate a therapeutic strategy to delay breathing compromise in those living with ALS by combining a selective adenosine 2A (A_2_A) receptor inhibitor (istradefylline) with AIH. The fundamental hypothesis guiding this proposal is that a single AIH trial after pretreatment with istradefylline enhances respiratory neuroplasticity versus AIH or sham intervention.

**Methods:**

We propose to evaluate resting breathing, respiratory strength, and participant-reported symptoms in adults living with ALS after combined istradefylline plus AIH. A mixed within- and between-participant study design incorporates 4 test sessions, separated by approximately 2 weeks (±5 days). Testing conditions include single sessions of AIH + istradefylline, AIH + placebo, sham AIH (ie, normoxia) + placebo, and sham AIH + istradefylline. Safety and feasibility will be characterized using the rate of adverse events, changes in vital signs, and participant-reported breathing sensations (Aim 1). Neuroplasticity of breathing and motor function will be evaluated as changes in resting breathing, voluntary respiratory strength, respiratory control, and maximal pinch force (Aim 2).

**Results:**

As of January 2025, with a target sample of 16 participants in each group, 10 participants with ALS and 5 control participants completed study procedures. Recruiting is ongoing, and the final participant will complete the study by December 2025. Publication of results is expected by the end of 2026.

**Conclusions:**

These aims will provide crucial data regarding the preliminary safety and feasibility of this paired intervention and help optimize therapeutic AIH as a rehabilitation strategy, thereby guiding further research concerning this novel treatment for ALS.

**Trial Registration:**

ClinicalTrials.gov NCT05377424; https://clinicaltrials.gov/study/NCT05377424

**International Registered Report Identifier (IRRID):**

DERR1-10.2196/76105

## Introduction

### Overview

Amyotrophic lateral sclerosis (ALS) is a progressive neurodegenerative disorder characterized by motor neuron death in the primary motor cortex, brain stem, and spinal cord, leading to muscular weakness and atrophy [1,2]. ALS can lead to progressive, variable weakness of the skeletal muscles involved in swallowing, speaking, coughing, limb movement, trunk control, and breathing. Respiratory muscle denervation causes diaphragm and accessory muscle weakness, hypoventilation, dyspnea, and orthopnea [3,4]. Ineffective airway clearance and aspiration result from bulbar denervation. Respiratory and bulbar dysfunction lead to the need for mechanical ventilation [5], shortened survival, and diminished quality of life [6]. Typical survival is 2-5 years post diagnosis [7]. Treatments that preserve or improve breathing would have a considerable impact on the duration and quality of life.

Acute intermittent hypoxia (AIH) consists of short, repeated exposures to mild or moderate hypoxia (9%-12% O_2_), separated by normoxic episodes (21% O_2_). Hypoxic episodes activate the carotid body chemoreceptors, sending chemoafferent signals to stimulate medullary respiratory neurons [8] as well as brain stem raphe neurons that contain the neurochemical serotonin. When this neural network is repeatedly stimulated during AIH [9], serotonin release from the raphe neurons triggers cell signaling pathways resulting in new synthesis of brain-derived neurotrophic factor protein. In turn, brain-derived neurotrophic factor strengthens synapses onto respiratory (and nonrespiratory) motor neurons [10-12], increasing respiratory motor output. AIH-induced motor plasticity was first described as a persistent enhancement of phrenic neural activity lasting hours after AIH has ended, an effect known as phrenic long-term facilitation (pLTF); a similar effect occurs in hypoglossal motor neurons [13,14]. pLTF is a form of activity-independent, neuromodulator-induced neuroplasticity that exhibits sensitivity to the pattern of hypoxic episodes and time of day [8,15,16]. Repeated AIH appears to amplify and prolong pLTF without detectable pathology [17-20], Thus, AIH may induce respiratory rehabilitation in ALS as well as other neurological conditions that compromise breathing [21].

Our group recently completed the first clinical trial of AIH administration in patients with ALS compared with unaffected controls. In this study, AIH enhanced tidal volume, minute ventilation, and collective respiratory muscle activation of participants living with ALS versus age- and sex-matched controls. Importantly, AIH was well-tolerated and free of treatment-related adverse effects; the participants typically could not distinguish between AIH versus sham AIH (ie, normoxia) [22].

While the modest AIH used in rehabilitation typically elicits motor facilitation via a serotonin-dependent mechanism (Gq protein–coupled receptor signaling [termed the “Q” pathway]) [8,14,23,24], an alternative AIH-induced signaling pathway results from adenosine (Gs protein–coupled receptor signaling [termed the “S” pathway]) [25-28], acting on adenosine 2A (A_2_A) receptors [29]. Serotonin and adenosine signaling oppose one another through powerful cross-talk inhibition; in extreme cases, this “battle” cancels phrenic motor plasticity [28,30-32]. Although both serotonin and adenosine receptors can be activated during mild hypoxia, the serotonergic “Q” pathway predominates. However, multiple personal characteristics, disease states, and treatment factors upregulate the adenosinergic “S” pathway, sufficiently to inhibit plasticity (Figure 1), including aging [33], low estrogen [33-35], inflammation [36], active phase delivery [37], genetic factors [33], and traumatic or neurodegenerative diseases [38].

In rodent models of spinal cord injury, an increased pLTF was observed after the administration of paired AIH and the A_2_A receptor inhibitor istradefylline [31]. In a subsequent clinical study, the impact of combined AIH and caffeine, a nonselective adenosine antagonist, found the combined approach further improved walking speed and distance in people with chronic spinal injuries [39]. Thus, combined AIH and A_2_A receptor antagonism may amplify respiratory motor plasticity [40]. However, since caffeine is a nonselective adenosine antagonist that also inhibits phosphodiesterase action, off-target effects such as nausea and elevated heart rate (HR) could limit its use in the doses needed to augment AIH plasticity. This study uses istradefylline for its greater affinity for the A_2_A receptor and its tolerance in clinical studies of older adults and those with Parkinson disease (PD).

**Figure 1 figure1:**
[figure not shown]
Competing serotonin- (Q) and adenosine-driven (S) pathways to phrenic motor facilitation. Listed on the right are factors that impact serotonin-dominant plasticity due to increased adenosinergic “S” pathway inhibition. By combining istradefylline with mild acute intermittent hypoxia (AIH), this protocol aims to minimize crosstalk inhibition by reducing S to Q pathway inhibition, allowing full expression of the “Q” pathway.

Elevated spinal adenosine is a characteristic of neurodegenerative diseases, such as ALS [41,42]. In the SOD1^G93A^ (copper zinc superoxide dismutase 1) mouse model of ALS, A_2_A receptor signaling contributed to motor neuron degeneration, while A_2_A receptor antagonism delayed disease progression [42]. A_2_A antagonism can also have neuroprotective and anti-inflammatory effects in motor neurons [43]. NOURIANZ (istradefylline) is a highly selective A_2_A receptor antagonist currently approved for use in adults with PD to offset inhibitory effects of upregulated A_2_A receptors on D2 dopamine receptors of the basal ganglia [44]. Istradefylline reduces daily “off” time in people with PD, improving periods of mobility, and is reported safe and well tolerated [45]. Dyskinesia (5%) and hallucinations (3.4%) were the most common side effects associated with longer-term use [46], but cognition, sedation, or risk of cardiovascular events were not impacted [47]. Considering the demonstrated safety of chronic istradefylline in PD and healthy controls, we hypothesize that this brief, temporary treatment will be safe in ALS.

We further hypothesize that the combination of istradefylline and AIH, in patients with ALS, will elicit greater gains in respiratory and nonrespiratory motor function than either intervention alone, and that will contribute to improvements in breathing and motor function. In a rodent model of phrenic motor neuron death, significant A_2_A receptor upregulation preceded motor neuron loss, but the coadministration of istradefylline improved motor neuron survival and maintained diaphragm function [43]. The information gained in this investigation will help us optimize intervention approaches for future studies of repeated, daily AIH as a rehabilitation tool. Thus, this study represents an important step in the iterative process of moving AIH protocols toward clinical practice.

### Aims

The objective of this study is to evaluate single and combined effects of selective A_2_A receptor antagonism and AIH on respiratory strength, resting breathing, and participant-reported symptoms in adults living with ALS and age-matched unaffected adults. The following two aims are proposed to test the hypotheses:

Aim 1: a single 20 mg istradefylline dose prior to AIH is safe and feasible. Dependent variables will include rate of adverse events (primary outcome), acute changes in vital signs (HR, respiratory rate, blood pressure [BP], etc), patient-reported symptoms (dyskinesias and dizziness), and study completion.

Aim 2: a single 20 mg istradefylline dose prior to AIH improves respiratory motor function when compared to either intervention alone. Dependent variables will include resting tidal volume (primary outcome), breathing rate and minute ventilation, respiratory muscle assessments via multichannel surface electromyography (sEMG), cough force, maximal inspiratory pressure (MIP), and maximal finger pinch force.

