### Aim 2 Dependent Variables

Quiet breathing assessment: the pneumotachograph and pressure transducer connected to the face mask will record breath-by-breath flow, tidal volume, airway opening pressure, and breathing rate. After achieving a stable tidal volume, minute ventilation will be recorded for 5 minutes. The primary outcome for Aim 2 is an increase in tidal volume from baseline to postintervention 120-minute follow-up. Minute ventilation will be measured at baseline, just prior to study gas delivery, and 60 and 120 minutes post gas intervention.Respiratory muscle assessment: sEMGs of the respiratory muscles and the abductor pollicis muscle (nonrespiratory control muscle) will be recorded as described above to assess effects of intervention on motor control. To identify the muscles active during the quiet breathing assessment, the root mean square of each muscle signal will be averaged. Multimuscle activation will be calculated using a validated, vector-based measure that indexes the magnitude and pattern of composite electromyography activity [58]. The composite respiratory muscle activity from each participant with ALS will be contrasted to the averaged composite magnitude and pattern of the pooled control sample [59]. It is anticipated that composite magnitude will be lower in people with ALS than in controls and increase with intervention, especially with combined AIH + istradefylline.MIPs: inspiratory force generation will be assessed as the maximal voluntary pressure generated by the inspiratory muscles (MIP) against a closed valve, measured at the mouth [60]. Sniff nasal inspiratory pressure measures inspiratory force generation at the nose. These tests will be used as surrogate measures of respiratory strength. Each test will be repeated until 3 measurements are obtained within 10% variability; a minimum 20-second rest will be provided between measurements. A recent systematic review reported a high level of evidence for concurrent validity for MIP; however, interrater reliability was low [61]. To minimize interrater reliability, we standardized instructions given to participants across sessions and used the same rater for each participant. MIP will be measured at baseline, immediately prior to study gas delivery (4 hours after drug administration), and 60 minutes post gas delivery. Sniff nasal inspiratory pressure will be measured at baseline, immediately prior to study gas delivery, and 120 minutes post gas delivery. We hypothesize that these measures will be lower in people with ALS than with controls and will increase with intervention, especially with combined AIH + istradefylline.Maximal airflow testing: peak airflows will be collected with a pneumotachograph attached to the face mask during maximal inspiration (maximum inspiratory flow) and voluntary coughing (peak cough flow). Tests will be repeated for 3-5 trials; at least a 30-second rest will be provided between measurements, but participants may rest as long as needed. Maximum inspiratory flow will be tested at baseline, just prior to study gas delivery, and 60 minutes post intervention. Peak cough flow will be tested at baseline, just prior to study gas delivery, and 120 minutes post intervention. We hypothesize that these measures will be lower in people with ALS than with controls and will increase with intervention, especially with combined AIH + istradefylline.Maximal voluntary pinch force: maximal static voluntary pinch force will be included as a nonrespiratory control. Pinch has been recognized as a sensitive marker of ALS disease severity due to preferential thenar wasting [62]. A recent study found fair to good test-retest reliability for this measure [63]. Pinch force will be evaluated in a seated position with the arm at the side in 90-degree elbow flexion and neutral forearm and wrist. The test will be repeated until 3 measurements are obtained with <10% variability, with a minimum 30-second rest between measurements. Pinch force will be measured at baseline, just prior to study gas delivery, and 120 minutes post gas intervention. We hypothesize that these measures will be lower in people with ALS than with controls and will increase with intervention, especially with combined AIH + istradefylline.

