### Sample Size, Data Management, and Statistical Analysis

The sample size calculation was based on pilot data from 8 adults with ALS showing ventilation changes in AIH versus a sham condition. The preliminary data showed 10.3% (SD 23%) larger tidal volume and 10% (SD 29%) greater minute ventilation 60 minutes post AIH, as compared to sham. Published work in rodent spinal cord injury models indicates that istradefylline paired with AIH greatly enhances improvement in diaphragm activity versus AIH or drug alone (effect size of combined approach: *d*=1.92).

Additional preliminary data using caffeine as a nonspecific adenosine receptor antagonist conservatively suggested a capacity for a 10% additional gain in ventilation. With 16 crossover participants, a repeated measures ANOVA comparing 4 conditions across 4 time points, with a pooled SD of 15.3, will be sensitive to detect a difference of power of >0.8 (*f*=0.31; *F*_3, 36_=2.86; ρ=0.5; α=.05). A target sample of 24 participants will account for potential attrition. The design includes age-matched unaffected adults as a comparator group.

Descriptive statistics, including frequencies, means, SDs, and medians, will be used when appropriate. Continuous variables will be summarized with descriptive statistics, and categorical variables will be summarized with counts and percentages. Demographics and disease-progression variables will be reported descriptively; while these are not included in a priori analyses of study aims, they may be used in an exploratory manner to interpret findings as appropriate. Change scores and percent change scores will be calculated from baseline for follow-ups at postdrug or placebo administration, 60 and 120 minutes after gas intervention. We will attempt to minimize missing data by planning the study procedures and proper biosignal acquisition, thoroughly documenting the study administration and data collection, and collecting the essential information to complete the study aims. Should missing data points still occur, statistically valid analyses that appropriately address the missing values are maximum likelihood, expectation maximization, and multiple imputation [64]. Any statistical code or algorithms developed to analyze acquired data will be available and shared upon request.

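### Aim 2 claims that the combination beats each intervention alone, but the only test named and powered is an omnibus ANOVA, so the stated power above 0.8 answers a different question

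*Protocol article*

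**What the plan says.** The hypothesis is specific and directional. Aim 2 (Introduction, Aims) says that "a single 20 mg istradefylline dose prior to AIH improves respiratory motor function when compared to either intervention alone". The Introduction, in the text after Figure 1, says that the combination "will elicit greater gains in respiratory and nonrespiratory motor function than either intervention alone", and the Discussion repeats the expectation. The endpoint is fixed under Aim 2 Dependent Variables: "The primary outcome for Aim 2 is an increase in tidal volume from baseline to postintervention 120-minute follow-up".

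Inference is mentioned once, under Sample Size, Data Management, and Statistical Analysis: "With 16 crossover participants, a repeated measures ANOVA comparing 4 conditions across 4 time points, with a pooled SD of 15.3", which "will be sensitive to detect a difference of power of >0.8". The parameters given are f = 0.31, a critical F of 2.86 on 3 and 36 degrees of freedom, a correlation of 0.5 and alpha 0.05. The rest of that section covers descriptive statistics, change scores and missing data.

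**The concern.** To support Aim 2, the combination must exceed AIH alone and must also exceed istradefylline alone, at 120 minutes. A test with 3 numerator degrees of freedom asks only whether any of the four conditions differs from any other, in either direction. An effect of AIH that is the same with drug and with placebo is enough to make it significant. Two of the four time points, baseline and 4 hours after the drug, also precede gas delivery.

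The AIH-only pattern is plausible: the Introduction reports that the group's earlier ALS trial already found a larger tidal volume after AIH. What this trial adds is the question of whether istradefylline contributes anything. The article gives a power figure for the omnibus question and none for that one, so a reader would credit 16 participants with more ability to answer Aim 2 than they have.

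**Working it through.** **Inputs from the article (Sample Size section).** 16 crossover participants; 4 conditions; pooled SD 15.3; correlation ρ = 0.5; f = 0.31; α = 0.05. Pilot AIH effect on tidal volume against sham 10.3% (SD 23%) at 60 minutes. Additional gain from adenosine antagonism 10%.

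**Assumptions.** Effects are in percent of baseline and correlation is equal across conditions. The pilot's 60-minute AIH effect, rounded to 10, persists to 120 minutes. The article does not say whether 15.3 is a per-condition SD or the SD of a difference. At ρ = 0.5 the two coincide, because SD of a difference = 15.3 × √(2 × (1 − 0.5)) = 15.3. The pilot SD of 23 serves as the upper end of the range.

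**1. The stated power.** Noncentrality λ = f² × N × m / (1 − ρ) = 0.31² × 16 × 4 / 0.5 = 12.30.
- With 3 and 36 df: critical F 2.866, power 0.805. This reproduces the article.
- With 3 and 45 df, the usual value for one group of 16 in a crossover: power 0.814. The choice of df hardly matters.

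**2. Omnibus test when istradefylline adds nothing.** True changes are 0, 0, 10, 10 for placebo + sham, istradefylline + sham, placebo + AIH and istradefylline + AIH. The spread of these means is 5, so f = 5 / SD. This is a one-way test on change scores with 3 and 45 df.

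| SD | f | λ = f² × 128 | P(omnibus significant) |
|---|---|---|---|
| 15.3 | 0.327 | 13.67 | 0.86 |
| 23 | 0.217 | 6.05 | 0.48 |

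At SD 15.3 the AIH-only f of 0.327 already exceeds the planned 0.31. In simulation of the same scenario, combination against AIH alone is significant in the favourable direction in about 2.5% of trials, the nominal one-tail rate.

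**3. The full 4-by-4 layout.** Suppose the AIH effect is present at only two of four times. The effect on a visit's mean is then 5, and the condition main effect depends on the residual correlation r between times within a visit: error variance = (1 − ρ) × SD² × (1 + 3r) / 4. The article gives no r.

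| r | SD 15.3 | SD 23 |
|---|---|---|
| 0 | 0.86 | 0.48 |
| 0.25 | 0.60 | 0.29 |
| 0.5 | 0.44 | 0.21 |
| 0.75 | 0.35 | 0.17 |

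The one-way figures are therefore at the high end for the main effect. Every entry is still well above 5%.

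**4. Power for the claim itself.** Paired t test, n = 16, two-sided 0.05 (critical t 2.131), additional gain 10. Noncentrality = 10 / SD × √16, which is 2.61 at SD 15.3 and 1.74 at SD 23. The joint column is a simulation under true changes 0, 0, 10, 20.

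| SD of difference | Combination vs AIH alone | Both contrasts | Completers for 80% (combination vs AIH alone) |
|---|---|---|---|
| 15.3 | 0.69 | 0.69 | 21 |
| 23 | 0.37 | 0.36 | 44 |

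Under the same hoped-for pattern the one-way omnibus test has power above 0.99 at SD 15.3 and 0.92 at SD 23. The gap between those figures and 0.69 or 0.36 is the gap between the two questions.

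**The case against.** The ANOVA appears only as the basis for sizing. Nowhere does the article make it the decision rule for Aim 2, and follow-up contrasts are commonly left to a statistical analysis plan, which is not shown here. This stands. A reader might infer that a significant omnibus F would be reported as success on Aim 2, or that the trial has no planned contrasts. The documents support neither.

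The endpoint is also not in doubt: 120 minutes is fixed, and change scores are planned for each follow-up. Only the power calculation spans all four times.

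The 86% comes from a one-way proxy and carries a 60-minute pilot effect to 120 minutes. This stands too, and the figure should not be read as a property of the 4-by-4 test.

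A reader might also see a second success criterion in the abstract's Objective, where the combination "enhances respiratory neuroplasticity versus AIH or sham intervention". That is weak evidence: it is one abstract sentence, and sham intervention can be read to include sham AIH with istradefylline. The Introduction, the Aims and the Discussion agree with one another.

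Finally, a two-by-two drug-by-gas analysis would suit the stated objective of single and combined effects, so two contrasts are not the only defensible choice. They are the direct translation of Aim 2 as worded.

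None of this removes the mismatch: the printed power belongs to a test that does not test the printed hypothesis, and contrasts in an unseen plan would not make that figure apply.

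**Conclusion.** The concern holds as a mismatch between hypothesis and sizing; it should be fixed. The arithmetic behind the power above 0.8 is sound, but it describes an omnibus comparison. For the comparison that decides whether istradefylline adds to AIH, power at 16 participants is about 0.69 if the SD of the paired difference is 15.3 and about 0.37 if it is 23. Requiring both comparisons gives about 0.69 or 0.36. These figures rest on the article's own 10% additional gain, on ρ = 0.5 and, for the joint figures, on an AIH effect of about 10% at 120 minutes.

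That AIH alone can make the omnibus test significant holds across the range examined. How often depends on a within-visit correlation that the article does not give. The trial is presented as preliminary and meant to inform later designs, which tempers the severity.

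**What to change.** In the Sample Size, Data Management, and Statistical Analysis section, define the primary Aim 2 analysis in participants with ALS as two paired contrasts on tidal-volume change from baseline to 120 minutes:

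- istradefylline + AIH against placebo + AIH;
- istradefylline + AIH against istradefylline + sham AIH.

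Support for Aim 2 requires both to be significant at two-sided 0.05 in the favourable direction. Because both are required, alpha need not be split. The omnibus ANOVA and the other time points become supportive. Replace the statement of power above 0.8 with the power of these contrasts at 16 completers, shown over the SD range 15.3 to 23, and say which SD 15.3 is.

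This changes no visit or procedure and does not require more enrolment. The cost is a criterion that is harder to meet than an omnibus test, and a less favourable power statement.
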